****):**

1. Adaptive pacing therapy + standardised specialist medical care (APT).

APT is based on the illness model of CFS/ME as a currently undetermined organic disease, with the assumption that APT can improve quality of life while not affecting the core disease other than providing the best conditions for natural recovery. APT is essentially an energy management approach, which involves assessment of the link between activity and subsequent symptoms and disability, using a daily diary, with advice to plan and pace activity to avoid exacerbations.

2. Cognitive behavioural therapy + standardised specialist medical care (CBT).

CBT is based on the illness model of fear avoidance, used in the three previous trials of CBT [39-41]. There are three essential elements: (a) assessment of illness beliefs and coping strategies; (b) structuring of daily rest, sleep, and activity, with a graduated return to normal activity; and (c) collaborative challenging of unhelpful beliefs about symptoms and activity.

3. Graded exercise therapy + standardised specialist medical care (GET).

GET is based on the illness model of deconditioning and exercise intolerance, used in the previous trials [42,43]. Therapy involves an assessment of physical capacity, negotiation of an individually designed home exercise programme with set target heart rates and times, and participant feedback with mutual planning of the next fortnight’s exercise programme.

4. Standardised specialist medical care alone (SSMC).

SSMC is given to all participants and includes visits to the clinic doctor with general, but not specific advice, regarding activity and rest management, such as advice to avoid the extremes of exercise and rest, as well as symptomatic pharmacotherapy. SSMC is standardised in the SSMC Doctor’s Manual. SSMC participants, like all other participants, will already have received the patient clinic leaflet (PCL). There will be no additional therapist involvement, and, in particular, there will be no diary monitoring with consequent advice.

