**As-treated sample** The as-treated sample is defined for the health economic analyses as all participants who were randomised into the trial and received one of the trial interventions. This sample will be a subset of the ITT sample, excluding participants who have not received any of the four interventions. Participants will be assigned to their received therapy rather than to their randomised intervention if these disagree.

##### 

**Safety sample** The safety sample is the ITT sample for this trial.

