##### **Departure from intended therapy (APT, CBT, GET)**

Departures from intended therapy refer to discrepancies between the intended therapy (as described in the therapy manuals) and the manner in which the therapies were actually delivered within the trial. To assess the extent of fidelity to the manuals as well as the distinguishability of the therapies, a random sample of audio recordings of therapy session number 10 will be independently and blindly assessed at the end of the trial. This will be done by competent therapists who do not have specific allegiance to any of the three forms of therapy. The sample will be of sufficient size to ensure that at least one tape from each therapist will be assessed. Each tape will be evaluated by two raters using a treatment integrity schedule specifically designed for the purpose. The scheme will be piloted using three tapes from each therapy, nine in total. Inter-rater reliability will be assessed and the ratings reported using descriptive statistics.

##### 

**Departures from randomised intervention policy** The overall definition of departures from the randomised intervention policy is given in terms of session attendance as:

a. Fewer than three sessions of SSMC (participants allocated SSMC only)

b. Fewer than ten sessions of APT, CBT or GET (participants allocated these therapies)

The number of sessions includes both face-to-face sessions and those conducted over the telephone. Within this definition, formal withdrawal from intervention after three sessions of SSMC or ten sessions of APT, CBT, or GET have been completed will not be regarded as a departure from the randomised intervention policy. However any participant withdrawing from his or her randomised intervention, or initiating another trial therapy prior to the above cut-offs would be regarded as a departure from the randomised intervention (it will be noted when this was by mutual consent). This includes participants randomised to SSMC who, in fact, receive APT, CBT or GET as a trial therapy. The overall compliance variable will therefore be binary separating those who followed their randomised intervention policy from those who did not.

The average (and range) of the numbers of therapy and SSMC sessions attended will be reported by intervention.

##### 

**Withdrawals from intervention** The decision to withdraw a participant from an intervention is made by the clinician or the participant (active withdrawals).

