**Method for handling compliance** The primary analysis will be based on the intention-to-treat principle which compares the randomised intervention policies rather than the interventions *per se*[48]. Interpretation of the extent to which intervention effect estimates reflect the effects of the intervention described in the protocol requires analyses focusing on the effects of the interventions received rather than the interventions prescribed. It is recognised that per-protocol analyses have a number of limitations, most importantly, selection biases resulting from participants who are excluded not being a simple random sample of those randomised. As such, discrepancies between the conclusions of an intention-to-treat analysis and a per-protocol analysis may not reflect discrepancies between the effects of the intervention prescribed and the intervention received. Acknowledging these and other limitations, a per-protocol analysis will serve as the primary sensitivity analysis investigating the robustness of the conclusions of the primary analysis to assumptions about departures from the randomised intervention policies.

#### **
*Descriptive analyses*
**

##### 

**Description of available data** The patterns of availability of baseline and follow-up data will be summarised overall and separately for the four interventions and for each assessment visit at the scale level. If one or more case report forms (CRFs) are available for a particular visit then the visit will be regarded as available. If one or more (non-administrative) items are available then the scale will be regarded as available. Availability of baseline and follow-up data will be summarised with differentiation of fully, or partially completed measures from those completely missing, or with sketchy detail.

The timing of baseline and follow-up data will be summarised overall and by intervention for each assessment visit in terms of the median (lower quartile, upper quartile, minimum and maximum) number of days from randomisation and the proportion falling outside guideline timeframes. Histograms of distributions will also be examined. Where assessments for a particular visit are carried out on more than one date, the timing of CFQ and SF-36PF assessments will be used to summarise visit timing. The extent to which visits are carried out on more than one date will be examined together with any further relevant details.

##### 

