##### **Health economics outcomes**

**Definition of outcome measures (including trial periods) Service use and lost employment** Comprehensive data are being collected on all health, social care and other relevant services used by individual study members using a tailored version of the Client Service Receipt Inventory (CSRI). The CSRI is used at baseline and at 24- and 52-week follow-up each time covering resource use for the previous 6 months. The CSRI covers the following broad categories of information.

• Living situation/accommodation

• Education, employment and income (including benefits)

• Time off work (measured in days) and time unemployed (or retired due to illness) summing the relevant cost period (−24 to 0 weeks, 0 to 24 weeks 0 to 52 weeks)

• Use of health and social care resources

##### 

**Cost calculation** The costs of each resource item will be calculated using best available unit cost estimates [75]. The cost of APT, GET and CBT will be estimated using information on the core resource inputs involved in delivering the interventions, and estimating country-specific costs for those inputs. Costs will be calculated using data on the number of intervention sessions received by each participant.

Lost employment costs for those in employment will be calculated by combining time off work with daily earnings. For those unemployed/retired due to ill health lost employment costs will be calculated by combining this period of time with average age and gender specific earnings.

The variables derived from the CSRI will be: (i) use (yes/no) of each service, (ii) number of service contacts/days in hospital, (iii) cost of each service, (iv) in employment (yes/no), (v) days not worked, and (vi) whether benefits received (each benefit - yes/no).

##### 

**Quality adjusted life year measurement** The EQ-5D consists of five domains (mobility, self-care, usual activities, pain/discomfort, and anxiety/depression). Each of these will receive a score of 1, 2 or 3 corresponding to no problems, moderate problems and major problems. Utility scores will be attached to each health state based on these scores (a table of utility values [76] has been produced by the Centre for Health Economics, University of York). These utility scores will be used to generate QALY gains over the follow-up period.

##### 

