**Cost-effectiveness analysis** Cost-effectiveness will be assessed by linking data on service cost differences and outcome (fatigue and physical disability) differences [77]. If any intervention has significantly lower costs and significantly better outcomes then it will be deemed to be more cost-effective. If costs are significantly higher and outcomes significantly better or if there is uncertainty in these findings (indicated by the CIs) then we will use the net benefit approach and cost-effectiveness acceptability curves to assess cost-effectiveness. Cost-effectiveness results will be plotted on a cost-effectiveness plane. This will involve producing estimates of cost and outcome differences from 1,000 bootstrapped re-samples of the original data. Such planes will be produced for each combination of two-way group comparisons. The plane will inform us as to the probability that an intervention has either (i) lower costs and better outcomes, (ii) lower costs and worse outcomes, (iii) higher costs and better outcomes or (iv) higher costs and worse outcomes than each comparator.

##### 

**Cost-utility analysis** This will be conducted in the same way as the cost-effectiveness analysis but will use quality adjusted life years (derived from the EQ-5D) as the outcome measure.

##### 

**Predictors of cost-effectiveness/cost-utility** The net-benefit approach allows multivariable analyses of economic data. This will enable us to identify predictors of cost-effectiveness and cost-utility. This will be done using regression models as described above. In particular we hypothesise that age and gender will predict cost-effectiveness and cost-utility.

##### 

**Baseline adjustment** The predictors of the cost regression model will be adjusted by the CSRI baseline outcome data.

##### 

**Model assumptions checks** Cost data are usually skewed and if this results in similarly skewed residuals then the standard linear model is inappropriate. The distribution of the regression residuals will be checked visually and if the distribution is non-normal we will use bootstrapping with 10,000 resamples to estimate 95% CIs around the cost differences (CIs will be based on the percentile or bias-corrected method depending on the level of bias observed in the model.) The assumption of independent residuals will be checked by bootstrapping at the therapist level.

##### 

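### The SAP ties an as-treated sample of unstated role to the health economic analyses, and states no baseline EQ-5D adjustment for QALY differences

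*SAP article*

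**What the plan says.** **Sample.** Under Trial samples, the SAP states: "The as-treated sample is defined for the health economic analyses as all participants who were randomised into the trial". Membership further requires that some trial intervention was actually received. The sample sits inside the ITT sample, "excluding participants who have not received any of the four interventions". The grouping rule follows: "Participants will be assigned to their received therapy rather than to their randomised intervention if these disagree".

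Switching is foreseen. The section on departures from randomised intervention policy counts crossovers as departures: "This includes participants randomised to SSMC who, in fact, receive APT, CBT or GET as a trial therapy".

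Elsewhere the SAP groups by randomisation. The Convention section says that, unless stated otherwise, an intervention means one of the four randomised groups. Method for handling compliance states: "The primary analysis will be based on the intention-to-treat principle". Intention to treat is repeated for the co-primary and secondary efficacy outcomes, and the safety sample is the ITT sample. The health-economics section names no sample. Its cost comparison is between the four interventions.

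**Baseline adjustment.** The health-economics paragraph on this reads, in full: "The predictors of the cost regression model will be adjusted by the CSRI baseline outcome data". On QALYs the SAP says: "These utility scores will be used to generate QALY gains over the follow-up period". Cost-utility is to be done in the same way as cost-effectiveness, from 1,000 bootstrap re-samples, with no covariate mentioned. Table 2 shows EQ-5D and CSRI collected at baseline, week 24 and week 52.

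**The concern.** An analyst who takes the sample definition at face value would regroup participants by what they received and leave out those who received nothing. People who switch or never start are selected after randomisation, so differences in cost, QALYs or net benefit between the regrouped arms could partly reflect who switched. The SAP recognises this hazard for the per-protocol analysis, warns of selection bias there, and keeps that analysis as a sensitivity analysis. It gives no such status to the as-treated sample. A second analyst, following the Convention section, would compare the groups as randomised. Both could claim to have followed the plan.

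There is a further consequence. Cost-effectiveness uses differences in fatigue and physical disability. If these come from as-treated groups, they may not match the intention-to-treat estimates of the same outcomes.

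The QALY point is separate. Baseline utility enters an area-under-the-curve QALY directly and also predicts later utility. Leaving it out of the model wastes information already collected and leaves the estimate open to whatever chance imbalance occurs.

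**Working it through.** The SAP gives no figure to reproduce on this point, so the check has a textual part and two illustrations.

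**1. Text side by side**

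| SAP section | How participants are grouped | Role |
|---|---|---|
| Convention | Randomised group, unless stated otherwise | General |
| Method for handling compliance | Intention to treat | Primary analysis; health economics not mentioned |
| As-treated sample | Therapy received; those who received nothing excluded | Tied to health economics; neither primary nor sensitivity stated |
| Cost comparisons | The four interventions | Primary economic method; no sample named |
| Health-economics sensitivity analyses | Not addressed | Informal care and lost-employment costs, therapy costs ±50% |

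The as-treated definition also gives no threshold for having received a therapy. Other sections use three or ten sessions (departures from policy) or one session (Participant flow).

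**2. What regrouping could do**

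Assume two equal arms and no true effect. A share f of SSMC participants receives one of the therapies and is moved to that arm. Movers differ from stayers by d in mean outcome, and both randomised arms have mean 0.

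- Stayers have mean −fd and movers (1 − f)d.
- The enlarged therapy group has mean f(1 − f)d/(1 + f).
- The false difference is f(1 − f)d/(1 + f) + fd = 2fd/(1 + f). By randomised group it is 0.

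| f (assumed) | d (assumed) | 2fd/(1 + f) |
|---|---|---|
| 0.02 | 0.1 | 0.004/1.02 = 0.004 |
| 0.05 | 0.1 | 0.010/1.05 = 0.010 |
| 0.10 | 0.1 | 0.020/1.10 = 0.018 |
| 0.10 | 0.2 | 0.040/1.10 = 0.036 |

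Neither f nor d can be taken from the SAP.

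**3. Baseline utility in the QALY**

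The trapezoid rule over weeks 0, 24 and 52 gives these weights:

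- baseline: (24/2)/52 = 12/52 = 0.231
- week 24: (12 + 14)/52 = 0.500
- week 52: 14/52 = 0.269

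With slope b of follow-up utility on baseline utility, a baseline difference D shifts the unadjusted QALY difference by D × (0.231 + 0.769b).

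The SAP reports 641 randomised to four arms, so about 160 per arm. The standard error of a chance baseline difference is SD × √(2/160) = SD × 0.1118. The SAP gives no utility SD or slope. I assume SD 0.20 to 0.30 and b 0.4 to 0.8.

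| SD | b | SE of imbalance | 0.231 + 0.769b | Shift at 1 SE |
|---|---|---|---|---|
| 0.20 | 0.4 | 0.0224 | 0.538 | 0.012 |
| 0.20 | 0.8 | 0.0224 | 0.846 | 0.019 |
| 0.30 | 0.4 | 0.0335 | 0.538 | 0.018 |
| 0.30 | 0.8 | 0.0335 | 0.846 | 0.028 |

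At 1.96 SE the range is 0.024 to 0.056.

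If QALY gains means area above the participant's own baseline, the multiplier becomes (0.231 + 0.769b) − 1, that is −0.462 to −0.154. The shift at 1 SE is then 0.003 (0.0224 × 0.154) to 0.015 (0.0335 × 0.462), in the opposite direction. Subtracting baseline therefore does not replace regression on it.

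**The case against.** The strongest reply is that the SAP never says the as-treated sample is primary or exclusive. The health-economics section does not invoke it, the Convention section makes the four interventions the randomised groups, and the intention-to-treat statement is general. This stands to the extent that one cannot say the plan abandons randomisation for its economic results. It does not remove the problem: a sample defined specifically for these analyses has no stated role, and no other sample is tied to them.

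A reader might infer two stronger points that the SAP does not support.

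- *Therapy-arm participants who never start therapy are moved into SSMC.* It is true that "SSMC is given to all participants and includes visits to the clinic doctor". But the grouping rule speaks of received therapy, and the Convention section limits that term to APT, CBT or GET. Participant flow counts one session of SSMC as initiating the randomised intervention. The move is at most one contestable reading, and no non-start rate is given from which to size it.
- *Costs and effects come from different groups.* Cost-effectiveness analysis draws cost and outcome differences from the same bootstrap re-samples, so within that analysis they share participants and grouping.

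On baseline EQ-5D, it is fair to answer that chance imbalance under randomisation is sampling error, which the confidence interval already reflects. That stands: this is lost precision and conditional exposure, not bias. One could also extend to QALYs the general rule under Stratification in the analysis, which adjusts for the baseline value of the outcome. But that rule is written for the primary analysis of therapy effect, and the specific health-economics paragraph mentions only cost.

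**Conclusion.** The point holds as two gaps in specification.

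First, the role of the as-treated sample is unstated and must be reconciled with the Convention section, the cost comparison between the four interventions, and the intention-to-treat principle. Used as the main sample, it would make the economic comparisons partly observational. The size cannot be derived from the SAP. Under the assumptions shown, a false difference runs from 0.004 with 2% of SSMC moved and d = 0.1 to 0.036 with 10% moved and d = 0.2. With few switchers it is small.

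Second, no baseline EQ-5D covariate is stated for QALY differences. Baseline utility has weight 12/52 in the area-under-the-curve QALY. A one-SE chance imbalance shifts the unadjusted difference by 0.012 to 0.028, assuming SD 0.20 to 0.30, slope 0.4 to 0.8 and 160 per arm. If groups were formed by therapy received, baseline differences could also be systematic.

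The primary efficacy and safety analyses are unaffected.

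**What to change.** In the health-economics section, state that the primary cost, cost-effectiveness and cost-utility analyses use participants as randomised (ITT). Keep the as-treated sample as a labelled sensitivity analysis, and define what counts as having received a therapy.

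Replace the baseline-adjustment paragraph with a rule for each outcome. Estimate QALY differences by regression on baseline EQ-5D utility and cost differences by regression on baseline CSRI cost, both with the four stratification factors, and refit these models within each bootstrap re-sample. State how QALY gains are calculated.

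The cost is SAP wording and some programming. Baseline EQ-5D, baseline CSRI and the stratification factors are already collected. Costing each participant by the number of sessions received, as the SAP plans, works equally well with participants grouped as randomised.

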##### **Other samples**

1. The sample screened for eligibility is defined as all consecutive new outpatients referred to PACE recruiting centres with a possible or definite clinical diagnosis of CFS/ME between 12 October 2004 and 14 November 2008.

2. The sample assessed for eligibility is defined as all patients consenting to formal eligibility assessment by the research workers.

3. The therapist sample includes all the therapists who were assessed for their competency in delivering trial therapies.

4. The doctor sample includes all the doctors signed up to deliver trial interventions.

5. The research worker sample includes all research assistants or research nurses collecting PACE trial data.

#### **
*Adherence to the protocol*
**

##### 

**Blinding of randomised interventions** The members of the Data Monitoring Committee, Trial Steering Committee and the trial statisticians were blinded to intervention allocation. Participants and all other research and therapy staff were not blinded, since it was impossible to do so. The steps taken to minimise and measure bias were:

1. Primary outcomes were self-rated by the participant.

2. Outcome assessments were coordinated by research workers not directly involved in the interventions participants received.

3. Equipoise was actively encouraged throughout the planning and course of the trial.

4. Baseline staff expectations regarding the outcome of the trial were recorded.

5. Participant intervention preferences and expectations regarding the outcome of their intervention were recorded.

##### **Departure from intended therapy (APT, CBT, GET)**

Departures from intended therapy refer to discrepancies between the intended therapy (as described in the therapy manuals) and the manner in which the therapies were actually delivered within the trial. To assess the extent of fidelity to the manuals as well as the distinguishability of the therapies, a random sample of audio recordings of therapy session number 10 will be independently and blindly assessed at the end of the trial. This will be done by competent therapists who do not have specific allegiance to any of the three forms of therapy. The sample will be of sufficient size to ensure that at least one tape from each therapist will be assessed. Each tape will be evaluated by two raters using a treatment integrity schedule specifically designed for the purpose. The scheme will be piloted using three tapes from each therapy, nine in total. Inter-rater reliability will be assessed and the ratings reported using descriptive statistics.

##### 

**Departures from randomised intervention policy** The overall definition of departures from the randomised intervention policy is given in terms of session attendance as:

a. Fewer than three sessions of SSMC (participants allocated SSMC only)

b. Fewer than ten sessions of APT, CBT or GET (participants allocated these therapies)

The number of sessions includes both face-to-face sessions and those conducted over the telephone. Within this definition, formal withdrawal from intervention after three sessions of SSMC or ten sessions of APT, CBT, or GET have been completed will not be regarded as a departure from the randomised intervention policy. However any participant withdrawing from his or her randomised intervention, or initiating another trial therapy prior to the above cut-offs would be regarded as a departure from the randomised intervention (it will be noted when this was by mutual consent). This includes participants randomised to SSMC who, in fact, receive APT, CBT or GET as a trial therapy. The overall compliance variable will therefore be binary separating those who followed their randomised intervention policy from those who did not.

The average (and range) of the numbers of therapy and SSMC sessions attended will be reported by intervention.

##### 

**Withdrawals from intervention** The decision to withdraw a participant from an intervention is made by the clinician or the participant (active withdrawals).

The number of active withdrawals (broken down by initiator (participant, clinical staff, both)) will be reported by intervention and centre, and by interval from randomisation. The most common reasons for withdrawal will be summarised.

